### Trial interventions

#### Excision with additional corticosteroid injections

Extralesional excision is performed with minimal margins, and absorbable monofilament sutures or permanent monofilament sutures are used for closure (Monocryl™, Ethilon™, Ethicon Inc, Somerville, NJ, USA). Surgery is performed by either surgical residents who have three years minimum experience, or by plastic surgeons. This standardised surgical procedure is not demanding, and we expect no learning curve. Many different surgeons (>20) reflect usual clinical practice in keloid treatment. After 2 weeks, an injection of triamcinolone acetonide 40 mg/ml is given in the newly formed scar. The injections can be repeated at 8 and 12 weeks postoperatively.

#### Excision with additional brachytherapy

Extralesional excision is performed with minimal margins, and absorbable monofilament sutures or permanent monofilament sutures are used for closure (Monocryl™, Ethilon™, Ethicon Inc, Somerville, NJ, USA). During the procedure, brachytherapy catheters are placed direct subcutaneously in order to cover the affected area. Next, a target dose of 600 to 900 cGy is given followed by one or two doses on the day of operation or the day after. After completion of brachytherapy, the catheter is removed. [24].

#### Intralesional cryotherapy

The Cryoshape needle (Etgar Group International, Kfar Saba, Israel) is positioned in the centre of the keloid to guarantee total coverage of the keloid when it is visually frozen. If necessary the Cryoshape needle is repositioned to achieve this. Our procedure differs slightly from Har-Shai *et al*. as we administer lidocaine with epinephrine around the keloid instead of intra- or translesional infiltration [21], because in our experience injecting through the keloid can be difficult and unnecessary painful for the patient. The cryotherapy can be repeated after three months if the desired effect has not been achieved.

During the study follow-up patients are not allowed to use additional keloid treatments. If treatment was not effective other treatments will be performed after at least 26 weeks follow-up. Follow-up measurements will continue as planned and patients will receive a request for an additional follow-up measurement 52 weeks after the additional treatment.

### Blinding

Neither physicians nor patients are blinded for treatment. They cannot be blinded due to surgery under local anaesthesia and differences in postoperative selfcare instructions. Furthermore, during the follow-up assessments, a physician or layperson would immediately recognize the treatment type by the resulting wound or scar.

### Safety concerns

Treatments applied in the current study are conventional rather than experimental. The hospital’s local safety procedures are followed. Possible side-effects are treated according to current best practice. No serious adverse events are expected; however, these will be reported to the Medical Ethics Committee supervising this study and registered with EudraVigilance within two weeks after the investigator is notified of such an event.

The protocol is approved by the Medical Ethics Committee of the Erasmus University Medical Centre Rotterdam and follows good clinical practice guidelines and current Dutch legislation.

### Outcomes

Our primary outcome measure is the Patient and Observer Scar Assessment Scale (POSAS), a 6-item patient questionnaire and a 6-item observer questionnaire. The patient and at least two observers (clinician and investigator) will independently assess the scar. The scores of the patient will range from 6 for the best imaginable scar to 60 for the worst scar imaginable, which is a PROM, the average of the observers scores will also range from 6 to 60. The score of the patient and observers will be added to form the total score that is our primary outcome, but the scores will also be analysed separately. A difference of six points on the total score is considered to be of clinical importance. The POSAS is a sensitive instrument that includes both physician and patient opinions of the scar, it has been previously validated, and performs well in a population of mostly dark-skinned keloid patients [25-29].

When one or two of the 12 POSAS items are missing at baseline we imputed the mean of the other scores of the same assessor. When a follow-up item was missing we imputed the last value carried forward. In cases where an item of the second observer was missing, we imputed the score of the first observer on the same item.

Secondary outcomes are keloid volume measured using a plaster mold, made before treatment, after the skin had completely healed at 12, 26 and 52 weeks. Time to recurrence is determined; the physician assesses recurrence at each follow-up visit; and, in case of recurrence, the patient is asked how many weeks after treatment the keloid recurred. As well as the diagnosis of keloid disease the diagnosis of keloid recurrence is a clinical diagnosis based on new growing scar tissue with features of keloid disease as described earlier. Photographs are taken at all visits, which will be used for additional (partial) observer scores on the POSAS and recurrence assessments. The additional observers will reduce bias in these outcomes. For assessing quality of life (QoL) we use a disease-specific and a general instrument: the Skindex-29 and the Short Form/RAND-36 (SF-36), respectively. The Skindex-29 was originally developed for psoriasis patients. It consist of 29 questions concerning symptoms, emotions and functioning and is, therefore, also suitable for other skin conditions. Questions are rated on a 5-point Likert scale. Scores range from 0 to 100, with 0 indicating no compromise on quality of life. A score ≥40 indicates a significant negative influence of the skin condition on QoL [30,31]. Worldwide, the SF-36 is the most frequently used general QoL questionnaire. It consists of 36 questions (scored on a Likert scale) addressing eight dimensions (vitality, physical functioning, bodily pain, general health perceptions, physical role functioning, emotional role functioning, social role functioning, mental health). The dimension scores are transformed to a 0 to 100 score, with a higher score indicating a higher QoL [32,33].

We will also analyse single item scores of our primary outcome measure POSAS, especially itch and pain from the patient questionnaire, and items on skin colour, pigmentation and vascularisation.

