### Patient recruitment

Patients who present with a keloid at an outpatient clinic of the four participating centres are considered for the study. A keloid is a clinical diagnosis and is distinguished from hypertrophic scars by the clinician’s judgement. The judgement between hypertrophic scars and keloid is based on: the growth history, starting early versus late after trauma, remaining stable versus still growing; shape, following initial lesion versus not following the initial lesion; and size, <0.5 cm versus >0.5 cm beyond the original lesion.

At a later stage, we will report how many patients with keloids were seen and how many were eligible for the study. Inclusion criteria are:

1. Keloid with a surgical indication.

2. One to three keloids that can be treated in one session.

3. Minimal size of 1 × 1 cm.

4. Suitable for excision and primary closure.

5. Patient aged between 18 and 75 years.

6. Fully mentally competent.

7. Sufficient knowledge of the Dutch or English language.

Exclusion criteria are:

1. Hypertrophic scars.

2. Scars after burn wounds.

3. Keloids less than one year old.

4. Pregnancy.

5. Use of systemic chemotherapeutics or chronic use of systemic corticosteroids or immunosuppressive medication.

6. Hypersensitivity for local anaesthetics, adrenaline, or triamcinolone (primary keloids).

7. Patients not sufficiently fit for brachytherapy (resistant keloids).

8. Severe comorbidity with life expectancy under one year.

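### Recurrence counts only new growth, so a stable keloid that cryotherapy never resolved is not an event, and the date of recurrence rests on unblinded patient recall

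*Protocol article*

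**What the plan says.** Recurrence is a secondary outcome. Under Outcomes, "the physician assesses recurrence at each follow-up visit", and the rule is that "the diagnosis of keloid recurrence is a clinical diagnosis based on new growing scar tissue with features of keloid disease as described earlier". The features meant are those under Patient recruitment: growth history, shape, and "size, <0.5 cm versus >0.5 cm beyond the original lesion". For time to recurrence, "in case of recurrence, the patient is asked how many weeks after treatment the keloid recurred".

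Under Intralesional cryotherapy the keloid is frozen where it lies, and "The cryotherapy can be repeated after three months if the desired effect has not been achieved". The same section adds that patients whose treatment was not effective may receive other treatment once at least 26 weeks have passed. Neither event is linked to the recurrence outcome. In the excision and corticosteroid arm, "The injections can be repeated at 8 and 12 weeks postoperatively", and this is not linked to recurrence either. No repeat is described for brachytherapy.

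On assessment, "Neither physicians nor patients are blinded for treatment" (Blinding), and "Photographs are taken at all visits, which will be used for additional (partial) observer scores on the POSAS and recurrence assessments" (Outcomes). The article says that these additional observers will reduce bias. Volume by plaster mould at weeks 12, 26 and 52, and POSAS at every visit, are collected in all arms.

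**The concern.** The two kinds of treatment leave the lesion in different states. Excision removes the keloid, so a keloid seen later has grown anew. Cryotherapy treats it in place, so a poor result can also be a keloid that never went away. A rule that requires new growth counts the first and misses the second. An identically worded event then means different things in the two arms being compared.

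The trial is meant to settle where cryotherapy belongs in stepped care and whether it could spare patients brachytherapy (Ethical issues). A lower recurrence rate after cryotherapy would be an obvious argument, and as planned it could arise partly from the definition.

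The dating is a second weakness. The diagnosis is made at fixed visits, but the event time comes from the memory of a patient who knows the treatment received.

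**Working it through.** **1. What the rule does to each course of events.** No arithmetic applies here; the sections are read side by side.

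| Course after treatment | Recurrence under the stated rule? |
|---|---|
| Excision, keloid returns with keloid features | Yes |
| Excision, regrowth without keloid features (hypertrophic) | No |
| Excision, steroid injections repeated at 8 or 12 weeks | No, not in itself |
| Cryotherapy, keloid regrows or keeps growing | Can be diagnosed as recurrence |
| Cryotherapy, keloid never resolves but is stable | No |
| Same, frozen again after three months | No |
| Same, given another treatment after week 26 | No |

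A patient can therefore follow the last three rows in turn and be recorded as recurrence-free at week 52. The protocol elsewhere treats non-response as a form of failure alongside recurrence. Under Background, care is stepped up for resistance or recurrence. Under Trial design, a keloid is resistant if it recurred after excision or did not respond to corticosteroids.

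**2. Dating.** Visits are at weeks 2, 12, 26 and 52, so the gaps are 12 − 2 = 10, 26 − 12 = 14 and 52 − 26 = 26 weeks. A diagnosis first made at week 52 after a clear week-26 visit places the event between weeks 26 and 52. If the patient recalls, say, week 20, the recorded time contradicts the physician's own finding at week 26. Nothing stated prevents this. The gaps are the widths within which visits locate an event; they do not limit the recall error.

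**3. Sample size, to see whether it is touched.** Inputs (Sample size calculation): difference 7.5 points, SD 15, correlation 0.75, alpha 0.05 (taken as two-sided), power 0.80, 25% loss, four groups.
- SD of a change score: 15 × √(2 × (1 − 0.75)) = 10.61.
- n per group: 2 × ((1.960 + 0.842) × 10.61 / 7.5)² = 31.4, so 32; with the t distribution 32.4, so 33.
- With loss: 33 / 0.75 = 44, and 44 × 4 = 176.

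This reproduces the stated 33 and 176. It rests on POSAS alone, so the recurrence definition does not affect it.

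**4. Illustration of size, on assumed inputs only.** The document gives no recurrence or non-response rate for the trial arms. Assume the same true failure proportion p in both arms, and that a share f of cryotherapy failures is stable non-resolution that is not counted. Apparent cryotherapy recurrence is then a = p(1 − f), and the spurious difference is d = pf. The chance of a significant result favouring cryotherapy, with n = 33 per arm, is Φ((d − 1.96 × SE₀) / SE₁), where SE₀ uses the pooled proportion and SE₁ the separate ones.

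For p = 0.30 and f = 0.50: a = 0.15, d = 0.15, pooled proportion 0.225.
- SE₀ = √(0.225 × 0.775 × 2/33) = 0.1028.
- SE₁ = √((0.30 × 0.70 + 0.15 × 0.85)/33) = 0.1011.
- Φ((0.15 − 0.2015)/0.1011) = Φ(−0.51) = 0.305, about 31%.

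| p | f | Apparent cryotherapy vs excision | Chance of significance |
|---|---|---|---|
| 0.20 | 0.25 | 15% vs 20% | 0.077 |
| 0.30 | 0.50 | 15% vs 30% | 0.305 |
| 0.50 | 0.75 | 12.5% vs 50% | 0.927 |

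Over p from 0.20 to 0.50 and f from 0.25 to 0.75, the spurious difference runs from 5 to 37.5 percentage points. The range shows that the effect could be negligible or decisive; it does not estimate it.

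**The case against.** The other side has several sound points.

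- **Recurrence and incomplete response are different constructs.** The protocol does not define failure as an outcome, and residual keloid is measured in every arm by volume and by POSAS, the primary outcome. This stands, and it limits the damage. It does not repair the recurrence comparison, which will be read in its own right.
- **A reader might infer that any regrowth after excision is an event.** It is not: the tissue must have keloid features. A poor scar after excision can also go uncounted.
- **A reader might infer that the definition must favour cryotherapy.** The documents support only that it can. A cryotherapy keloid that resumes or continues growing may be diagnosed as recurrence, and the share of stable non-responders is unknown.
- **A reader might see repeat cryotherapy as a one-sided loophole.** In the primary-keloid part, repeat steroid injections are not events either, and permitted repeats belong to the assigned treatment. The contrast is cleaner in the resistant part.
- **Photograph observers are a stated safeguard.** They are, but they are not said to be blinded, no other definition is given for them, and they do not supply the date.
- **Recall affects only the date.** Correct: the recurrence rate is untouched by it. The article names no time-to-event method, and an analysis plan not shown here may reconcile recalled weeks with visits. Yet the article does fix the patient's answer as the source of the date.
- **Counting any tissue present at week 52 as failure would turn the bias round**, because excision removes the tissue at the outset. This stands and shapes the fix.

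**Conclusion.** The point holds for a secondary outcome. As written, the recurrence rule does not mean the same thing after cryotherapy as after excision, and a stable non-responder who is then given another treatment can be recorded as recurrence-free. The comparison can favour cryotherapy, most clearly against excision with brachytherapy. The size cannot be derived from the document, and the illustrated range rests wholly on assumed failure and non-counting proportions. Separately, the recurrence week is open to recall error in an open trial and can contradict an earlier recurrence-free visit. The primary outcome and the 176 patients are unaffected. The change should be made, since a lower recurrence rate after cryotherapy would otherwise be hard to interpret.

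**What to change.** - Keep recurrence as defined, and state that a lower rate after cryotherapy will not be interpreted on its own.
- Add a supportive treatment-failure outcome, worded alike in all arms: recurrence, or receipt of another keloid treatment because the assigned one was not effective, or no response on a residual-volume criterion from the week-52 mould. Fix that criterion in advance; mere presence of tissue should not count.
- Report protocol-permitted repeats, both cryotherapy and steroid injections, descriptively and not as failures.
- Analyse time to recurrence as interval-censored between the last visit without and the first visit with physician-diagnosed recurrence. Use the recalled week only in a sensitivity analysis.

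The cost is wording and analysis on data the trial already plans to collect, provided that treatment given for ineffectiveness is recorded. No visit, treatment rule or sample size changes. The downsides are slightly less precise timing and a supportive outcome less comparable with published recurrence rates, which is why recurrence itself stays reported.

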### Data collection

Data are collected at baseline, before randomisation, and at follow-up assessments 2, 12, 26, and 52 weeks after treatment. The questionnaires are preferably filled out online, although a paper version is also available. All paper questionnaires are scanned and stored on a secure disk. The online questionnaires are saved by the online questionnaire program, and a backup is made regularly.

Photographs are taken at all visits. Volume of the keloid is measured at baseline and after the skin has completely healed at 12, 26, and 52 weeks after treatment.

### Statistical analysis

Baseline demographic and clinical characteristics will be presented as proportions or means and standard deviations (SD) where appropriate. Because of the longitudinal data with multiple influencing factors, a sophisticated model is necessary. Mixed models (also called multilevel linear regression analysis) is a technique that efficiently uses longitudinal data and can work with patients’ data even though measures at certain time points may be missing.

The units of analysis are the repeated measurements of the patient (first level), not the keloid, because we use several QoL measures that are not measurable for the unit keloid. The second level will be the individuals participating in the study. If necessary, a third level of subgroups with specific characteristics (skin type, duration of keloid disease and location of the keloid) can be added. If the third level is shown to improve the fit of the model, it will be incorporated in the model. We will use backward elimination and start with an unstructured covariance structure for intercept and time (slope). Simplifications of the random part of the model will be tested using the deviance statistic with restricted maximum likelihood. For the fixed part we will postulate a saturated model. We take in account time, logarithm of time and squared time, treatment condition and its interactions with time. Nonsignificant effects will be excluded using Wald tests. The fit of the final fixed model will be compared with the saturated model and will be checked using ordinary maximum likelihood. When characteristics like sex, age, skin type, duration of keloid disease and location of the keloid make a significant contribution to the model, they will be incorporated in the model [34-37]. Differences between treatment effects will be expressed in terms of effect sizes, standard errors and *P* values. Effect sizes will be calculated by dividing the estimated differences by the estimated standard deviation. An effect size of 0.20 is considered a small effect, 0.50 a medium effect and 0.80 as a large effect [38].All analyses will be performed on an intention-to-treat basis. IBM SPSS version 21.0 and SAS version 9.3 will be used to perform the analyses.

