**Methods/Design:**

This is a multicentre, randomised controlled open trial that compares 1) intralesional cryotherapy versus excision and corticosteroids for primary keloids, and 2) intralesional cryotherapy versus excision and brachytherapy for therapy-resistant keloids. The primary outcome is the Patient and Observer Scar Assessment Scale (POSAS), a 12-item scale (with score 12 indicating the best and 120 indicating the worst scar imaginable). A difference of six points on the total score is considered to be of clinical importance. Secondary outcomes are recurrence rates, volume reduction, Skindex-29 scores, SF-36 scores and complication rates. Primary and secondary outcome measurements are taken at baseline, and at 2, 12, 26 and 52 weeks postoperatively. For analysis, a linear mixed model is used. A total of 176 patients will be included over a period of 2.5 years. The protocol is approved by the Medical Ethics Committee of the Erasmus University Medical Centre Rotterdam and follows good clinical practice guidelines.

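### With baseline as a modelled outcome, the fixed part called saturated has at most four mean parameters per arm for five POSAS measurements, so the planned fit check cannot detect misfit of the time curve

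*Protocol article*

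**What the plan says.** The Statistical analysis section specifies the fixed part in two sentences, which begin "For the fixed part we will postulate a saturated model. We take in account time, logarithm of time and squared time". The second sentence in full is "We take in account time, logarithm of time and squared time, treatment condition and its interactions with time". Terms are then removed ("Nonsignificant effects will be excluded using Wald tests"), and the end point of that reduction is judged as follows: "The fit of the final fixed model will be compared with the saturated model and will be checked using ordinary maximum likelihood". No model with visit as a category is named.

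The number of measurements is given twice. The abstract has "Primary and secondary outcome measurements are taken at baseline, and at 2, 12, 26 and 52 weeks postoperatively", and the Data collection section has "Data are collected at baseline, before randomisation, and at follow-up assessments 2, 12, 26, and 52 weeks after treatment". Keloid volume is the exception, with baseline and three later measurements.

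The Statistical analysis section takes the repeated measurements as the first-level units. The covariates it names are sex, age, skin type, duration and location; the baseline score is not among them.

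**The concern.** A saturated mean model has one free mean per arm per visit, so it reproduces any pattern of means exactly. That property is what makes it a yardstick: a simpler model that fits nearly as well can be trusted, and one that does not is rejected.

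A four-parameter curve over five measurements lacks this property. If the true treatment difference has a shape that the curve cannot follow, the starting model and every reduction of it miss the same feature. The likelihood comparison can then show that too many terms were removed, but not that the curve was inadequate from the start. The label would also tell readers that lack of fit had been excluded when it had not been examined. At stake are the estimated POSAS differences at the visits where the curve bends most, against the six points that the Outcomes section regards as clinically important.

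**Working it through.** **Inputs.** Measurement times t = 0, 2, 12, 26, 52 weeks (abstract; Data collection). Fixed terms: intercept, t, log t, t², with treatment interactions (Statistical analysis). Effect 7.5 points, SD 15, correlation 0.75 and 33 patients per group (Sample size calculation).

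**The plan's own figure.** The sample size does not depend on this point, and it reproduces. The SD of change is 15 × √(2 × (1 − 0.75)) = 10.61. A two-sided t-test for 7.5 points at 80% power needs 33 per group; 33/0.75 = 44; 44 × 4 = 176.

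**Parameter count.** A saturated model needs 5 means per arm, or 10 per two-arm comparison. The listed terms give at most 4 per arm, or 8.

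**Rank.** Log t is undefined at t = 0 and the article gives no offset, so log(t + c) is assumed. The matrix [1, t, log(t + c), t²] at the five times has rank 4 of 5 for every offset tried (0.01 to 1, in weeks and in months). On the four follow-up visits alone, [1, t, log t, t²] has rank 4 of 4.

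**Effect on the fitted difference.** Assume balanced data and an interaction of treatment with every time term. One contrast k of the five visit differences lies outside the curve. The fitted difference is then μ − k(k′μ)/(k′k), where μ is the true difference. The fitted values are the same under exchangeable correlation and under the random intercept and slope covariance that was tried.

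Worked example, c = 0.5 week: k = (−0.317, 0.824, −1, 0.588, −0.095), and k′k = 0.100 + 0.679 + 1 + 0.346 + 0.009 = 2.134.

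- Step from week 2, μ = D(0, 1, 1, 1, 1): k′μ = 0.317 D, and 0.317/2.134 = 0.1485. Week 12: 1 + 0.1485 = 1.15 D. Week 26: 1 − 0.588 × 0.1485 = 0.91 D. Week 52: 1 + 0.095 × 0.1485 = 1.01 D.
- Onset at week 12, μ = D(0, 0, 1, 1, 1): k′μ = −0.507 D, and −0.507/2.134 = −0.2376. Week 12: 1 − 0.2376 = 0.76 D. Week 26: 1 + 0.588 × 0.2376 = 1.14 D. Week 52: 1 − 0.095 × 0.2376 = 0.98 D.

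Range over c = 0.1, 0.5 and 1 week:

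| True difference | Week 12 | Week 26 | Week 52 |
|---|---|---|---|
| D from week 2 on | 1.09–1.18 D | 0.90–0.94 D | 1.01–1.02 D |
| D from week 12 on | 0.74–0.79 D | 1.12–1.16 D | 0.97–0.98 D |
| D at week 2 only | 0.36–0.39 D (truth 0) | about −0.22 D (truth 0) | about 0.04 D (truth 0) |

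For D = 7.5, the first two profiles err by 0.7 to 2.0 points at week 12, 0.4 to 1.2 at week 26 and at most 0.2 at week 52. The week-2-only profile puts 2.7 to 2.95 points at week 12, where there is no difference. A smooth profile, 7.5 × (1 − exp(−t/10)), is fitted to within 0.45 points at every visit.

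**Fit check.** The final and starting models both lie in the space of the same four columns. The contrast k is in neither, so comparing their likelihoods says nothing about it.

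**Linear interaction only.** If the treatment difference is, or is reduced to, intercept plus t, the step from week 2 is fitted as 0.74 D at week 12 and 1.14 D at week 52. The onset at week 12 is fitted as 0.48 D and 1.24 D.

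**The case against.** The strongest reply is that the text may be literally correct. Log time does not exist at time zero, there are four follow-up visits and there are four mean terms. With baseline left out of the outcome vector and all interactions included, the model is saturated and needs no offset. The article does not say outright that baseline is an outcome, and its covariate list is open-ended. This stands as a condition on the point. Baseline as outcome remains the natural reading, because the repeated measurements are the first-level units, five are listed, and the baseline score is not a named covariate.

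Second, the harm on the full-interaction reading is modest. With 33 completers per arm and SD 15, the standard error of a difference at one visit is 15 × √(2/33) = 3.7 points, larger than the curve errors in the table. Growth curves are an accepted choice, and saturated may simply mean the fullest candidate model. This stands too. It limits the point to the label and the check, and gives no ground for banning the curve.

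Three stronger readings are tempting but not supported:

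- A reader might infer that the planned model can push a week-52 difference across six points, since 5 × 1.24 = 6.2. That needs an interaction with linear time only. Three listed time terms, interactions in the plural and the word saturated all point to full interactions at the start. The linear form could still be reached by Wald elimination.
- A reader might infer that these treatments produce the pattern such curves fit worst. The article gives no POSAS time course after excision, and its Table 1 describes a cryotherapy cohort without a week 2 value. A difference confined to week 2 fits worse than either a step or a late onset.
- A reader might treat six points as a decision rule. The Outcomes section calls it clinically important, not a criterion for success.

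**Conclusion.** The point holds, on the condition that baseline is among the modelled outcomes. The benchmark is then not saturated: it is one mean parameter short per arm, and the planned comparison cannot reveal misfit of the curve.

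With full interactions, balanced data and a log offset of 0.1 to 1 week, the two sustained profiles are distorted by 9 to 26% at week 12, 6 to 16% at week 26 and under 3% at week 52. The risk therefore lies mainly in abrupt differences at weeks 2 to 26. A week-52 error of up to 24% in these profiles arises only with an interaction in linear time alone. The profiles are illustrations, because the article gives no expected course for the treatment difference. Keloid volume, with four measurements, is not affected at the starting model, and neither is the sample size. The change should be made because the planned safeguard does not do what its name promises; nothing here shows that the one-year result would be wrong.

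**What to change.** In the Statistical analysis section, define the saturated reference as scheduled visit, as a categorical factor, with a full treatment-by-visit interaction. Test the curve in time, log time and squared time against that reference by maximum likelihood. If the curve shows lack of fit, take the visit-specific treatment differences from the categorical model. State in the same place whether baseline is an outcome and, if it is, how log time is defined there.

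Cost: a few sentences, one extra mean parameter per arm and slightly less precision where the categorical model is used. No extra data or patients are needed, and the curve can stay as the summary if it passes the test.
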